## Abstract

**Introduction:**

The Rehabilitation Training (ReTrain) intervention aims to improve functional mobility, adherence to poststroke exercise guidelines and quality of life for people after stroke. A definitive randomised controlled trial (RCT) is required to assess the clinical and cost-effectiveness of ReTrain, which is based on Action for Rehabilitation from Neurological Injury (ARNI). The purpose of this pilot study is to assess the feasibility of such a definitive trial and inform its design.

**Methods and analysis:**

A 2-group, assessor-blinded, randomised controlled external pilot trial with parallel mixed-methods process evaluation and economic evaluation. 48 participants discharged from clinical rehabilitation despite residual physical disability will be individually randomised 1:1 to ReTrain (25 sessions) or control (exercise advice booklet). Outcome assessment at baseline, 6 and 9 months include Rivermead Mobility Index; Timed Up and Go Test; modified Patient-Specific Functional Scale; 7-day accelerometry; Stroke Self-efficacy Questionnaire, exercise diary, Fatigue Assessment Scale, exercise beliefs and self-efficacy questionnaires, SF-12, EQ-5D-5L, Stroke Quality of Life, Carer Burden Index and Service Receipt Inventory. Feasibility, acceptability and process outcomes include recruitment and retention rates; with measurement burden and trial experiences being explored in qualitative interviews (20 participants, 3 intervention providers). Analyses include descriptive statistics, with 95% CI where appropriate; qualitative themes; intervention fidelity from videos and session checklists; rehearsal of health economic analysis.

**Ethics and dissemination:**

National Health Service (NHS) National Research Ethics Service approval granted in April 2015; recruitment started in June. Preliminary studies suggested low risk of serious adverse events; however (minor) falls, transitory muscle soreness and high levels of postexercise fatigue are expected. Outputs include pilot data to inform whether to proceed to a definitive RCT and support a funding application; finalised Trainer and Intervention Delivery manuals for multicentre replication of ReTrain; presentations at conferences, public involvement events; internationally recognised peer-reviewed journal publications, open access sources and media releases.

**Trial registration number:**

NCT02429180; Pre-results.

Strengths and limitations of this studyThis pilot randomised controlled trial study meets the Medical Research Council (MRC) guidance on the development and evaluation of complex interventions and includes comprehensive patient and public involvement.This preliminary evaluation of a late stage rehabilitation programme addresses the gap in the evidence related to what facilitates stroke recovery in the longer term.This small scale study is designed to estimate effect sizes but has insufficient statistical power to detect differences in outcomes between groups.The follow-up period is relatively short compared with what would be planned for a fully funded definitive trial.

## Introduction

Residual physical disability is common following discharge from stroke rehabilitation services. A third of first-time stroke survivors remain physically disabled 5 years after their stroke,^1^ equivalent to more than 300 000 people in the UK (ref. 2, p. 51). Stroke services are traditionally ‘front loaded’ with provision tailing off a few months after stroke.^3^ However, people with stroke report a variety of unmet long-term needs and a sense of being abandoned by National Health Services (NHS).^4^ The England National Stroke Strategy recommends that stroke be regarded as a long-term condition and that continuing support is provided for those who need it.^5^ This includes community-based rehabilitation, with an emphasis on personalisation, reablement and self-management of the consequences from stroke.^5^ There is good evidence that exercise can promote functional recovery,^3^ enhance adjustment and coping,^6^ improve psychological well-being,^6^ and reduce the risk of recurrence.^7^ Hence, stroke guidelines recommend that people with stroke should regularly engage in specific forms of exercise;^8^
^9^ however, many individuals do not meet these recommendations.^10^
^11^ Various personal and environmental factors may account for this: stroke-related impairments, lack of confidence or knowledge regarding exercise and its benefits, and inadequate provision of support programmes and facilities. In response, community-based programmes are being offered;^12–14^ however, these programmes often focus on fitness rather than function, giving little attention to self-management or to sustaining behaviour (to ensure benefits are maintained after structured programmes have ended). National stroke guidelines^8^ recommend interventions address functional improvement^15^ and self-management^16^ strategies even though a recently updated Cochrane review^17^ notes the gap in evidence regarding these interventions.

An approach called Action for Rehabilitation from Neurological Injury (ARNI) attempts to address these concerns; it was created specifically for people with stroke and acquired brain injury who wish to continue their functional recovery.^18^ ARNI is not a rigidly defined programme but a set of principles and strategies tailored to individual circumstances and contexts. It is led by registered exercise professionals who have been additionally trained and accredited by the ARNI Institute (http://www.arni.uk.com). Our research into ARNI started because a stroke survivor participating in PenCLAHRC's (http://clahrc-peninsula.nihr.ac.uk/) research question generation process asked if ARNI worked but, as yet, there have been no randomised controlled trials (RCTs) of this intervention. In the UK, the NHS, some local authorities and other organisations are using ARNI trainers to provide community-based training for stroke survivors. We surveyed known providers of this training including those located in Northeast England, Lancashire, Luton and Bedfordshire, Milton Keynes, Hillingdon and Cornwall. The survey found that training has been very positively received by stroke survivors, their families and clinicians but it varied in content and delivery (unpublished report: [name], 2011). Reports of benefits by the broadcaster Andrew Marr have also increased public awareness of ARNI.^19^ However, the evidence for ARNI remains largely anecdotal, it may only work for a selected few and the approach is difficult to reproduce. There is a need for a more detailed cohesive specification of ARNI that could be rigorously evaluated and replicated. Thus, we have followed the Medical Research Council's framework for the development and evaluation of complex interventions^20^ and have undertaken five linked preliminary studies: (1) the aforementioned survey of current ARNI provision in the UK, (2) a comparison of the ARNI approach with relevant stroke practice guidelines,^9^ (3) before-and-after studies of group-based^21^ and (4) one-to-one^22^ training, and (5) focus groups conducted with our participants.^23^ From this work we have designed a programme called Rehabilitation Training (ReTrain) which is based on core ARNI principles and informed by best practice guidelines for stroke.^9^ Before undertaking a large definitive RCT of ReTrain a pilot study is needed to address issues of feasibility and acceptability.

### Aims

To undertake a study that will evaluate the feasibility and acceptability of procedures to inform the design and delivery of a definitive RCT of ReTrain (which would assess the clinical and cost-effectiveness of ReTrain for stroke survivors). The study objectives are to: (1) assess the feasibility and acceptability of recruitment, randomisation, allocation concealment and outcome assessment blinding procedures; (2) obtain an estimate of the outcome variance and retention rates to inform sample size calculations for a fully powered trial; (3) confirm the feasibility of ReTrain, its acceptability to participants and finalise the ReTrain Trainer and Intervention Delivery manuals; (4) assess outcome measurement burden for participants to confirm that data can be collected (including safety data), measures will be completed and to inform selection of primary and secondary measures for the definitive trial; (5) rehearse process evaluation methods for the definitive trial, including assessment of intervention fidelity (ie, adherence to the intervention manual by participants and trainers); (6) evaluate resource use, including carer support, and costs associated with intervention delivery, assess the feasibility of collecting health and social service resource use and explore the relative strengths of measures uses to calculate health-related quality of life (quality-adjusted life years, QALYs) and provide an economic evaluation framework for the definitive trial.

## Methods and analysis

### Design

A two-group, assessor-blinded, randomised controlled external pilot trial with parallel mixed-methods process evaluation and economic evaluation. Eligible participants will be individually randomised 1:1 to intervention (ReTrain) or control (exercise advice booklet).^24^ The design is depicted in figure 1, which shows the flow of one cohort of participants (the study comprises three programmes).

**Figure 1 BMJOPEN2016012375F1:**
[figure not shown]
Study flow chart.

#### Population

Potential participants will be included if they meet the following inclusion and exclusion criteria: they have (1) a primary clinical diagnosis of stroke (assessed by referring clinician/general practitioner (GP) records), (2) they are at least 1 month (but no upper limit) since discharge from NHS physical rehabilitation services at randomisation, (3) they are able to walk independently indoors with or without mobility aids, but have self-reported difficulty with or require help on stairs, slopes or uneven surfaces, (4) a willingness to be randomised to either control or ReTrain and to attend the training venue, (5) have cognitive capacity and communication ability sufficient to participate in the study (assessed by recruiting team using standard tools).^25^

Criterion (3) has been selected pragmatically to maximise eligibility while ensuring participants have a mobility deficit that could be addressed by the intervention. Eligible people with aphasia will not be excluded.

Potential participants will be excluded if they are <18 years old, currently (or within 1 month of) receiving ARNI-based training or have contraindications to moderate-to-vigorous physical activity (adapted from American College of Sports Medicine (ACSM) guidelines)^26^ including:
Acute or uncontrolled heart failure;Unstable or uncontrolled angina;Uncontrolled cardiac dysrhythmia causing symptoms or haemodynamic compromise;Symptomatic severe aortic stenosis;Current deep vein thrombosis, pulmonary embolus or pulmonary infarction;Acute myocarditis or pericarditis;Suspected or known dissecting aneurysm;Unstable/uncontrolled blood pressure;Systolic blood pressure >160;Diastolic blood pressure >100;Acute systemic infection;Uncontrolled diabetes.

#### Sample size

The target recruitment number is 48 participants (24 per group). This number is based on the recommendation of 30 complete data sets for pilot studies in order to estimate outcome variance^27^ and running the intervention three times (Exeter I and South Devon, then Exeter II, ie, 3×8 patients) to enable investigation of variations in context and other process variables. This recruited number also allows estimation of a predicted attrition rate of 20% with a precision of ±5% with 95% certainty.

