#### Data analysis

Given the feasibility objectives of this pilot study, the focus of data analysis will be descriptive. For both recruitment settings (Exeter and South Devon) participant flow will be summarised using the CONSORT flow diagram, reporting recruitment and attrition rates (both treatment and study drop-outs) with 95% CIs. The diagram will also reflect the number of recruitment letters sent, numbers consenting, number randomised, number undertaking intervention and number of completed outcomes alongside means and SDs regarding the number, length and frequency of sessions. All protocol deviations, along with reasons and number of missing items on questionnaires will be reported. Mean and SDs (or equivalent) for all clinical outcomes for both study arms will be reported at baseline, 6 and 9 months follow-up. For the trial process evaluation, we will use a thematic analysis for the qualitative interview data and use several of the quantitative measures (including demographic, medical and questionnaire data) to help identify and understand potential mediators and moderators of trial outcome. For the analysis of intervention fidelity, we will use the procedures we designed and tested in our preliminary studies for the video analysis combined with trainer interview data and the session checklists (that will be part of the Intervention Delivery manual). These data collection and analysis methods will be assessed for their potential to inform the process evaluation component of a definitive trial. In such a future trial, the health economics analysis will be a cost-utility analysis, using QALYs and secondary analyses will investigate the benefits of the intervention more broadly within the framework of a cost consequences approach, so offering the potential to weight different outcomes in a multicriteria decision analysis framework.^51^ In this pilot study, we will assess the relative benefits of calculating health-related quality of life using SF-6D developed from the SF-12 over the QALY calculated using EQ-5D-5L; explore the psychometric properties of the SF-12 and investigate whether it has greater ability to discriminate between the milder health states. We will assess costs associated with intervention delivery as well as assess the feasibility of collecting health and social service resource use through a Service Receipt Inventory. Any missing data in the Inventory will be recorded and we will check if any resource use categories are misunderstood by matching Inventory completion with medical records for a subgroup of participants. This will help us develop strategies to minimise missing data in a future definitive trial.

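### The sample size section claims ±5% precision at 95% for a 20% attrition rate; 48 participants give about ±11 percentage points

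*Protocol article*

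**What the plan says.** The Sample size section sets the target: "The target recruitment number is 48 participants (24 per group"). It gives two bases for that number: a recommendation of 30 complete data sets for estimating outcome variance, and three runs of the intervention with eight places each. It then adds a precision statement: "This recruited number also allows estimation of a predicted attrition rate of 20% with a precision of ±5% with 95% certainty".

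Two other places bear on this. In Aims, the second objective is to "obtain an estimate of the outcome variance and retention rates to inform sample size calculations for a fully powered trial". In Data analysis, the article commits to "reporting recruitment and attrition rates (both treatment and study drop-outs) with 95% CIs".

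**The concern.** The sentence supplies every input needed to check it: the number of participants, the expected proportion, the half-width and the confidence level. These four do not fit together. With fewer than 50 people and a proportion of 20%, a 95% interval cannot be as narrow as ±5 points.

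It matters because retention is one of the quantities the pilot exists to estimate, and it sets the allowance for loss in the later trial. A reader who accepts the sentence would take an observed 20% to mean a true rate between 15% and 25%. The data will support a range more than twice as wide. If the sentence is carried into a funding application, it misstates what the pilot can show.

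**Working it through.** **Inputs, all from the Sample size section**

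- n = 48, the recruited number. The sentence ties its claim to this number, so a larger screened or approached denominator is excluded.
- p = 0.20, the predicted attrition.
- Stated half-width d = 0.05.
- Confidence 95%, taken as two-sided because of the ± sign and the 95% CIs planned in Data analysis.

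**Attempt to reproduce the stated figure**

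Standard error = √(p(1 − p)/n) = √(0.2 × 0.8/48) = √0.003333 = 0.0577, or 5.8 points.

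95% half-width = 1.96 × 0.0577 = 0.113, or 11.3 points. The interval is 8.7% to 31.3%.

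Ratio to the stated figure = 11.3/5 = 2.26. The stated ±5 is not reproduced.

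**What ±5 points would mean or require**

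- Confidence carried by ±5 points at n = 48: z = 0.05/0.0577 = 0.866, and 2Φ(0.866) − 1 = 0.61.
- Number needed for ±5 points at 95%: 1.96² × 0.16/0.05² = 245.9, so 246.
- Attrition rate at which 48 people would give ±5 points at 95%: about 3.2%, far from the predicted 20%.

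**Other readings tried**

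| Reading | Half-width (points) |
|---|---|
| Wilson, 9 to 10 losses of 48 | 10.9 to 11.3 |
| Jeffreys, 9 to 10 losses | 10.9 to 11.3 |
| Agresti-Coull, 9 to 10 losses | 11.1 to 11.5 |
| Clopper-Pearson (exact), 9 to 10 losses | 11.8 to 12.3 |
| Normal with continuity correction | 12.4 |
| One-sided 95% (two-sided 90%) | 9.5 |
| 80% level | 7.4 |
| One standard error | 5.8 |
| Finite population correction, N = 3000 (the stroke survivors cited under Participant recruitment) | 11.2 |
| n = 38 (48 less 20%) | 12.7 |
| n = 30 | 14.3 |
| n = 24 (one arm) | 16.0 |

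Reading ±5% as relative to 20%, that is ±1 point, would need about 6147 participants. At exactly 20% of 48 (9.6 losses), the Wilson limits are 11.1% and 33.3%.

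**Effect on the allowance for loss**

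The later trial's recruitment is multiplied by 1/(1 − attrition). At 20% this is 1/0.80 = 1.25. Over the implied range of 15% to 25% it runs from 1/0.85 = 1.18 to 1/0.75 = 1.33. Over 8.7% to 31.3% it runs from 1/0.913 = 1.10 to 1/0.687 = 1.46.

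**Check on the choice of 48**

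48 × 0.80 = 38.4, which still exceeds the 30 complete data sets sought.

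**The case against.** The arithmetic is hard to contest, so the best case for the plan concerns consequence.

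First, the attrition statement is an added property of a number already fixed on other grounds. The section bases 48 on complete data sets and on intervention places, and both survive the correction. This stands. A reader might infer that the sample size is unjustified, or that the pilot should grow to 246. The document supports neither, because nothing in it makes ±5 points a design requirement.

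Second, Data analysis promises confidence intervals for attrition. The true uncertainty will therefore be visible in the results, and those planning the later trial can work from the observed interval. This also stands, and it limits the harm. It does not make the planning statement true, and the reported intervals can be expected to contradict it.

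Third, the article never says that the pilot could tell 20% attrition from 30%, and it states no progression threshold for attrition. Attributing such a claim to it goes beyond the text.

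Finally, since 5 is near one standard error, a reader might conclude that the authors omitted the 1.96 multiplier. The article gives no derivation, and one standard error is 5.8, which rounds to 6. The origin of the figure is unknown.

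**Conclusion.** The point holds as an error in one stated figure. With 48 participants and 20% attrition, the 95% half-width is about 11 percentage points, so the article overstates the precision by a factor of about 2.26. The result assumes a simple binomial proportion over all 48 recruited and a two-sided interval. Every 95% alternative tried leaves it well above 5 points; even the one-sided reading gives 9.5.

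The error bears on what the pilot can deliver for its second objective. It does not affect the target of 48, the design or any planned analysis. How cautiously the later trial should set its allowance for loss is a choice for that trial and not a correction to this protocol.

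**What to change.** Replace the precision sentence in Sample size with:

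> With 48 participants, an attrition rate of 20% would be estimated with a 95% CI half-width of about ±11 percentage points (about 9% to 31% by the normal approximation; Wilson interval about 11% to 33%).

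Each range should stay labelled with its method, because the Wilson interval is not centred on 20%. The cost is one sentence and a less favourable stated figure. No extra participants are needed, and no procedure or analysis changes.

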#### Participant recruitment

Participants will be recruited and the programme delivered in two areas of Devon (Exeter and South Devon). These areas cover a population of 250 000 with at least 3000 stroke survivors who require the help of others in everyday activities.^11^ To maximise potential recruitment, several routes for recruitment will be used to reach both those who are just leaving rehabilitation services and those who have been discharged for some time:
Via clinicians in NHS primary care, hospital and community stroke services:
Early supported discharge teams;Community rehabilitation teams;Physiotherapy outpatients departments;Those responsible for conducting the 6-month review recommended by the National Stroke Strategy;GP surgeries via the local Clinical Research Network (CRN).

Clinicians will provide potential participants with an invitation letter and brief description of the study and, if they are interested, obtain permission to pass on their details to the study team. The clinician will ask the potential participant to complete a short form (or complete the form on their behalf), recording their contact details and consenting for these details to be passed to the research team.
Direct (using contacts)
The CRN (formerly South West Stroke Research Network (SW SRN)) using hospital-based recruitment team, newsletters and targeted mailing;Exeter Clinical Research Facility which maintains a database of health research-interested members of the public;Letters, articles and posters will be used to provide brief details of the study and invite expressions of interest to contact the research team by telephone call, email or post.Promotion via local stroke support networks identified through national organisations such as the Stroke Association, Different Strokes and Connect, and via internet searches and in local media.Word of mouth, study flyers, adverts and information sheets.

We have discussed recruitment plans with two local community rehabilitation team leads and the CRN (who have checked three GP surgery's databases); from this we estimate a recruitment rate of 5–6 participants per month although this is one of the feasibility objectives being tested in this study. Our preliminary Devon-based studies recruited 2–4 participants per month, but only from the Exeter area, without formal network support, using fewer routes, and based on narrower inclusion criteria to the current proposal.

A potential issue in recruitment is the likelihood of attracting people who are already committed to exercise and not those who are currently inactive, who may be put off by the emphasis on the term ‘exercise’. Focus groups conducted previously by the research team, and our Service User Group (SUG), have suggested that promotion should emphasise the potential functional and quality of life benefits, and not promote it primarily as physical exercises. To this end, a member of the research team will brief and support the personnel involved in providing initial information about the study to potential participants, and where necessary spend time in contact with potential participants to help their understanding of the intervention and study. For those who are already committed to exercising, they will still be eligible providing they are no longer involved in a formal rehabilitation programme. Because of uncertainty in recruitment rates and patterns and the need to have eight people ready to start the training programme, some participants may have to wait several weeks until sufficient group members have been recruited. To help mitigate the potential problem of excluding those who do not live close to a venue, reasonable travel costs (eg, mileage claims, local bus and train journeys, and specialised wheelchair taxis) to and from the training venue will be offered to all participants.

